#### Data analysis of the main outcome measure

The main outcome measure is treatment effect, and this categorical variable includes improvement, stabilization, and deterioration. Stabilization and deterioration will be merged into a new variable, namely non-improvement. Hence, this three-level classification will comprise merged binary variables and include improvement and non-improvement. For this dichotomous variable, Breslow-Day method, CMH, GEE, and logistic regression will be utilized to compare curative effects between the two groups.

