### Outcomes

#### Primary outcome

The main outcome measure is the treatment effect, which will measure the classification indicators, such as improvement, stabilization, and deterioration levels. This three-level classification will monitor changes in TLC, VC, DLCO, SaO_2,_ and PaO_2._ The specific classification criteria will be as follows:

Improvement: after treatment of subjects, an increase in the TLC or VC by 10%, an increase in DLCO by 15%, an increase in SaO_2_ by 15%, and an increase in PaO_2_ by 4 mm Hg (1 mmHg = 0.133 kPa), compared to the pre-treatment values.

Stabilization: the health status of subjects between improvement and deterioration.

Deterioration: after treatment of subjects, a decrease in the TLC or VC by 10%, a decrease in DLCO and SaO_2_ by 15%, and a decrease in PaO_2_ by 4 mm Hg (1 mmHg = 0.133 kPa), compared to the pre-treatment values.

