#### Information collection from participants during each follow-up

Each subject enrolled in the study will be followed-up once every 3 months and the described indices will be determined each time. A total of 5 (months 0, 3, 6, 9, and 12) determinations per subject will be made during the study period.

In each follow-up, a structured questionnaire will be used to collect clinical information and indices. These included cough, expectoration, fatigue, chest tightness, chest pain, dyspnea, insomnia, emaciation, loss of appetite, VC, TLC, FVC, FVC%, DLCO, DLCO%, FEV1, RV, MVV, RV/TCL, ERV, IRV, PEF, MMEF, VT, IC, 6-min walking distance, Borg dyspnea score, and TCM syndrome scores, which are reflective of respiratory function and will help determine TCM syndrome scores. Moreover, the SCL-90, SF-36, SAS, and SDS scales will be used to record and measure quality of life for each individual during every follow-up.

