#### Principles of data analysis

Statistical analysis will be performed using the SAS Analytics Software Solutions (version 9.4, SAS Institute Inc., Cary, North Carolina 27,513, US). Odds ratio (OR) and 95% confidence interval (*CI*) of categorical variables will be calculated using two-tailed Chi-square test, and Fisher’s exact test will be used to compare the differences in qualitative variables between the two groups. Quantitative variables will be described as the mean, median, standard deviation, or inter-quartile range, and analyzed using the rank-sum test, t-test, analysis of variance (ANOVA), repeated measurement ANOVA, generalized linear mixed model (GLMM), and generalized estimation equation (GEE). Differences will be considered significant at *P* < 0.05 with two-tailed test.

This study will be conducted across several research centers; some subjects from the same center, it may produce similarity or homogeneity. The methods that will be considered for adjusting for effects of the center will include the Breslow-Day method, Cochran-Mantel–Haenszel statistics (CMH), and logistical regression, whereas GEE and GLMM will be used for data mining. In addition, confounding factors will be considered in all data analysis, it will include gender, age, and other lung diseases.

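### Breslow-Day is misassigned as a treatment comparison and a centre adjustment, GEE has two conflicting roles, and no single procedure decides the primary outcome

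*Protocol article*

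**What the plan says.** Under Data analysis of the main outcome measure, the three-level outcome is reduced to two levels: "Stabilization and deterioration will be merged into a new variable, namely non-improvement". The article then names the methods: "For this dichotomous variable, Breslow-Day method, CMH, GEE, and logistic regression will be utilized to compare curative effects between the two groups". None is called primary.

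Under Principles of data analysis, the centre effect is addressed: "The methods that will be considered for adjusting for effects of the center will include the Breslow-Day method, Cochran-Mantel–Haenszel statistics (CMH), and logistical regression". The same sentence continues: "whereas GEE and GLMM will be used for data mining". That section also sets a single criterion, P < 0.05 two-tailed.

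The Primary outcome section compares values after treatment with values before it and names no month. The definition begins "Improvement: after treatment of subjects, an increase in the TLC or VC by 10" per cent. The follow-up section states: "A total of 5 (months 0, 3, 6, 9, and 12) determinations per subject will be made during the study period". Table 1 gives pirfenidone and both granules for 12 months.

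The sample size section sets up superiority by a margin of 0.10. Randomisation is stratified by centre.

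**The concern.** The sentence that fixes the primary analysis gives one of its four methods a job it cannot do. The null hypothesis of Breslow-Day is a common odds ratio across centres. A significant result means that the effect differs between centres, and it can occur with no overall benefit. A non-significant result is what one expects when the treatment works equally well everywhere. Listing it as a centre adjustment is a second error, because it produces no adjusted estimate.

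The other three methods are not ranked, and the two sections disagree on whether GEE is confirmatory or exploratory. A reader of the final report could not tell from this article which p-value was meant to decide the trial.

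**Working it through.** **1. The plan's own figure.** The article gives no error rate for the primary analysis. Its related figure is 233 per group. Inputs from the sample size section: control 0.533, treatment 0.767, d = 0.767 − 0.533 = 0.234, margin 0.10, printed z values 1.64 and 1.28.

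N = 2 × [(1.64 + 1.28)/(0.234 − 0.10)]² × 0.533 × 0.467 = 236.4, against 233 printed, a difference of 3.4/233 = 1.5%. The figure is close enough, so 233 per arm is used below.

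**2. What Breslow-Day responds to.** It sums over centres the squared gap between the observed treated responders and the number expected under the common Mantel-Haenszel odds ratio, each divided by its variance. The sum is referred to chi-square with (centres − 1) degrees of freedom. The common odds ratio is fitted out, so its size does not move the test.

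At the planned rates the odds ratio is (0.767/0.233)/(0.533/0.467) = 2.88. Simulation used 4,000 trials per scenario, 233 per arm and two-sided 0.05. Assumptions not in the article: 5 or 10 equal centres, and a between-centre SD of 0.4 on the logit scale. Proportion of trials rejecting at month 12:

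| Scenario | Centres | CMH | Breslow-Day |
|---|---|---|---|
| No effect | 5 | 0.046 | 0.049 |
| No effect | 10 | 0.049 | 0.054 |
| Odds ratio 2.88 in every centre | 5 | 1.000 | 0.052 |
| Odds ratio 2.88 in every centre | 10 | 0.9995 | 0.061 |

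The Monte Carlo standard error near 5% is √(0.05 × 0.95/4000) = 0.0034. Breslow-Day rejects at about the same rate whether or not the treatment works.

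**3. Error rate if Breslow-Day is read as efficacy.** CMH and Breslow-Day are asymptotically independent under no effect, so the chance of at least one rejection is 1 − 0.95² = 0.0975. Simulated with CMH, Breslow-Day and logistic regression together: 0.092 (5 centres) and 0.100 (10 centres). CMH or logistic regression without Breslow-Day: 0.046 and 0.049, the same as CMH alone. The logistic model was run unadjusted. GEE was not simulated, so its contribution is not quantified.

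**4. GEE in two places.** The general principles place GEE with GLMM under data mining. The main-outcome section lists GEE as one of four methods for the primary comparison. Elsewhere the article uses GEE for the TCM syndrome response over months 0, 3, 6, 9 and 12. If that use carried over, the primary comparison would span several visits, whereas CMH and logistic regression would ordinarily use one.

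**5. Visit.** Treatment lasts 12 months, so months 3, 6 and 9 fall during treatment and month 12 is the first visit after it. The secondary and quality-of-life sections list all the time points; the primary section lists none. Both facts fit a single month-12 assessment.

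**6. The margin.** The sample size hypothesis is a difference above 0.10. An ordinary CMH test addresses no difference. At the planned rates with 233 per arm, ignoring centre, the standard error of the risk difference is √[(0.767 × 0.233 + 0.533 × 0.467)/233] = 0.0428. The expected lower 95% limit is 0.234 − 1.96 × 0.0428 = 0.150. The chance that this limit exceeds 0.10 is Φ(0.134/0.0428 − 1.96) = Φ(1.17), about 88%, against at least 99.9% for CMH against no difference. The two readings of the primary test are therefore not interchangeable.

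**The case against.** The best defence is that a condensed article may list methods and leave the deciding one to the analysis plan, and that the centre paragraph speaks only of methods to be considered. Breslow-Day is a normal companion to CMH, and the authors may have meant it as one. Data mining may be loose wording, since GLMM and GEE are the stated methods for secondary outcomes. GEE could also be meant to cluster by centre rather than by visit.

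Much of this stands. Silence about a lead test would not be a finding by itself. But the article is not silent: it gives Breslow-Day two functions that it does not have, and it gives GEE two roles. An unseen plan cannot make those sentences correct.

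A reader might infer four stronger points, which the document does not support:

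- **Patients who die leave the comparison.** Nothing says so. The classes rest on measured change, but non-improvement can naturally include anyone not shown to improve, a full analysis set is planned, and the handling of deaths may be in the analysis plan.
- **The visit is a free choice among four.** Under an assumed within-patient correlation of 0.6, taking CMH at any of four visits gave 15.5 to 16.3% false positives, and any of three tests at any visit 30 to 32%. These figures require an open visit, and the text points to month 12.
- **Logistic regression inflates the error further.** Beside CMH it added nothing in the simulation.
- **The trial's error rate is 9.75%.** That holds only if a Breslow-Day rejection is declared as benefit, which the wording permits but does not say will happen.

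**Conclusion.** The point holds in a limited form. Breslow-Day is wrongly assigned in both places, which follows from what the test is and needs no assumption. GEE's role is contradictory between the two sections, and its presence blurs a visit that otherwise reads as month 12. No procedure is named as decisive.

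The size is conditional: about 9.75% instead of 5% at one visit if Breslow-Day is counted as an efficacy test beside CMH, resting on asymptotic independence and supported by simulation under assumed centre numbers and centre variation. This is a defect to correct before analysis. It does not show that the trial will reach a wrong conclusion.

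**What to change.** Name one primary analysis: the CMH test stratified by centre, which is the randomisation stratum, of improvement versus non-improvement at month 12 in the full analysis set, reported with the Mantel-Haenszel risk difference and 95% CI.

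Reconcile it with the sample size section in one of two ways: compare the lower confidence limit with the 0.10 margin, or state that the test is of no difference. On the figures above, the first has about 88% power with 233 evaluable per arm.

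Describe Breslow-Day only as a check that odds ratios are homogeneous across centres, and remove it from the treatment comparison and the centre adjustment. Label logistic regression supportive; it can carry the covariates (gender, age and other lung diseases) that the article wants considered. Label GEE supportive too, and make the general principles and the main-outcome section agree on it.

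The cost is a few sentences, with no new patients or data. The downside for the investigators is losing the freedom to choose among methods after seeing the results. With CMH as the single test, simulated type I error was 0.046 (5 centres) and 0.049 (10 centres).

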#### Data analysis of secondary efficacy indices

For each subject from the treatment and control groups, the quantitative indicators of respiratory function (TLC, VC, DLCO, FVC, FVC%, VT, IC, 6-min walking distance, and Borg dyspnea score) will be collected several times and GLMM will be performed to determine the effectiveness of therapeutic modalities in a continuous time frame (0, 3, 6, 9, and 12 months).

The treatment effect in TCM syndrome includes clinical cure, notable effect, effectiveness, and ineffective. The clinical cure, notable effect, and effectiveness will be merged into a new variable named “total effective”. Hence, the treatment effect in TCM syndrome will comprise two new dichotomous variables, the qualitative variables, namely, “total effective” and “ineffective,” and will be recorded in each subject when they consult a physician across the time points in the study (0, 3, 6, 9, and 12 months). Hence, GEE will be conducted to determine the efficacy of treatment between the two groups.

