#### Secondary outcome measure

*(1) Indices reflecting respiratory function*

Certain variables will be monitored for each subject during every follow-up, including VC, TLC, FVC, FVC%, DLCO, DLCO%, FEV1, RV, MVV, RV/TCL, ERV, IRV, PEF, MMEF, VT, and IC.*(2) Six-minute walking distance and Borg dyspnea score*

The quantitative variable of 6-min walking distance and the Borg dyspnea score will be obtained for each subject in each observation.*(3) Quality of life assessment indices*

The SCL-90, SF-36, SAS, and SDS scales will be used to collect the score (quantitative variable) for each subject during each visit.*(4) Evaluation standard of treatment effect in TCM syndrome*

The treatment effect in TCM syndrome will be divided into four categories based on the guiding principles for clinical research of the new TCM (Trial) (2018 year). The categorical variables are clinical cure, notable effect, effective, and ineffective. The specific classification criteria are as follows:

Clinical cure: a reduction rate of TCM syndrome scores ≥ 95%;

Notable effect: a reduction rate of TCM syndrome scores to between 70 and 95%.

Effective: a reduction rate of TCM syndrome scores to between 30 and 70%.

Ineffective: a reduction rate of TCM syndrome scores < 30%.

The reduction rate of TCM syndrome scores(%) = (pre-treatment TCM syndrome scores-post-treatment TCM syndrome scores) / TCM syndrome scores × 100%

The total effective rate(%) = (clinical cure cases + notable effect cases + effective cases) / total cases × 100%.

The data will be analyzed to determine if there are significant differences between the treatment and control groups after treatment, if there are significant differences in the treatment group pre- and post-treatment, and if there are significant differences in the control group pre- and post-treatment.

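### The only analysis the plan assigns to the TCM syndrome outcome is a two-level cut at a 30% reduction, which gives up power for modest effects although the score is collected at every visit

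*Protocol article*

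**What the plan says.** Three places in the protocol article bear on this.

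- **Collection.** The section on information collected at each follow-up lists "6-min walking distance, Borg dyspnea score, and TCM syndrome scores, which are reflective of respiratory function" and fixes the schedule: "A total of 5 (months 0, 3, 6, 9, and 12) determinations per subject will be made during the study period".
- **Definition.** Item (4) of the secondary outcome measures turns the percentage reduction in the score into ordered grades: "The categorical variables are clinical cure, notable effect, effective, and ineffective". The boundaries are 30%, 70% and 95%; the lowest grade reads "Ineffective: a reduction rate of TCM syndrome scores < 30"%. The same item defines a total effective rate, which pools the top three grades.
- **Analysis.** The section on secondary efficacy indices merges those three grades: "The clinical cure, notable effect, and effectiveness will be merged into a new variable named “total effective". It lists the resulting two-level variable at months 0, 3, 6, 9 and 12, and concludes: "Hence, GEE will be conducted to determine the efficacy of treatment between the two groups". In the same section the quantitative indicators sent to a GLMM are "TLC, VC, DLCO, FVC, FVC%, VT, IC, 6-min walking distance, and Borg dyspnea score". The TCM syndrome score is not among them. The next section sends the four quality-of-life scales to a GLMM on the ground that they are quantitative.

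**The concern.** The named comparison sees only whether a patient crosses the 30% line. A treatment that moves patients from *effective* to *notable effect* or *clinical cure* produces no signal, because all three grades are one category. The plan defines cure as a grade but names no between-group comparison that could detect a difference in it.

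All subjects are selected for Qi-Yin deficiency, and the Discussion makes TCM syndromes part of the efficacy evaluation, so this outcome matters to the trial's purpose. Both arms also receive active background treatment. If that alone brings most controls past 30%, the two-level variable has little room left to separate the arms. A modest real benefit could then be reported as no difference, although the data to show it had been collected.

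**Working it through.** **Plan's own figure.** There is none for this outcome: no expected rates, SD or power. The only size figure is 233 per group, raised to 257 for 10% loss to follow-up. Analysed per arm: 257 × 0.90 = 231.3, taken as 231.

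**Assumptions (none is in the plan).** Percentage reduction normally distributed, SD 30 points in both arms; true shift d = 0.25 SD (7.5 points); control total effective rate p0 of 53.3%, 80% or 90%. The 53.3% is borrowed from the control response rate in the sample size section and belongs to a different outcome. One visit. The test is two-sided at 0.05, as in the principles of data analysis.

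**Formulas.**
- Binary cut: p1 = Φ(Φ⁻¹(p0) + d); power = Φ((p1 − p0)/√[(p0(1−p0) + p1(1−p1))/n] − 1.96).
- Four grades: tie-corrected rank test, normal approximation, on the category probabilities from cuts at 30, 70 and 95.
- Full score: power = Φ(d√(n/2) − 1.96).
- Capped score: the same comparison of means after setting values above 100% to 100%.

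**Worked case, p0 = 0.80.**
- Binary: Φ⁻¹(0.80) + 0.25 = 0.842 + 0.25 = 1.092, so p1 = 0.8625. SE = √[(0.160 + 0.1186)/231] = 0.0347. Power = Φ(0.0625/0.0347 − 1.96) = Φ(−0.16) = 0.44.
- Full score: 0.25 × √(231/2) = 2.687. Power = Φ(2.687 − 1.96) = Φ(0.727) = 0.77.

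| Control rate | Treated rate | Binary | Four grades | Full score | Full score, capped |
|---|---|---|---|---|---|
| 53.3% | 63.0% | 0.568 | 0.656 | 0.766 | 0.765 |
| 80% | 86.3% | 0.436 | 0.695 | 0.766 | 0.756 |
| 90% | 93.7% | 0.310 | 0.694 | 0.766 | 0.738 |

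The capped score gains 0.765 − 0.568 = 20 points at the lowest control rate and 0.738 − 0.310 = 43 points at the highest. The four grades gain 9 to 38 points.

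**Sensitivity.**
- *SD.* With SD 20 the four-grade power is 0.61–0.64, so at a 53.3% control rate the gain over the binary cut is only about 4 points. The uncapped full-score result does not depend on the SD.
- *Large effect.* Carrying the primary endpoint's 76.7% v 53.3% across gives d = Φ⁻¹(0.767) − Φ⁻¹(0.533) = 0.646. At that shift the binary power is about 1.00 for a 53.3% control rate, 0.99 for 80% and 0.90 for 90%; the other analyses are at about 1.00.
- *Benefit above the cut only (invented rates).* If both arms are 80% total effective but cure is 10% v 25%, the planned comparison has nothing to find, while a comparison of cure rates at 233 per arm has 99% power.

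**Month 0.** The reduction is (pre − pre)/score = 0, below 30%, so every subject is *ineffective* at that visit by definition. It carries no information on treatment.

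**The case against.** The strongest reply is that the document does not rule out analysing the score. A reader might infer that the score will be analysed only as a yes/no variable, and the text does not support that. The principles of data analysis list methods for quantitative variables in general, GLMM among them. Directly after the TCM formulas, the secondary outcomes section promises between-group tests and pre/post tests within each group. Grades built from change since baseline cannot themselves be tested pre against post, so that sentence may well mean the score. This stands: both passages leave room. Neither commits to an analysis of the score or of the four grades, while the specific section names the binary GEE.

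Absence from the GLMM list is also weak evidence taken alone. The list is headed as respiratory function and leaves out FEV1, RV, PEF and other declared secondary indices, so it is plainly abbreviated. The point therefore rests on what is assigned to the TCM outcome and not on the omission.

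The total effective rate is defined in the same item that cites the TCM guiding principles, and the primary outcome is also merged to two levels. The responder measure is a legitimate, consistent choice. That is a reason to keep it, though not a reason to name nothing else.

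Finally, every power figure is assumed. At a 90% control rate with SD 30 the control mean is 30 + 30 × 1.28 = 68, and about 15% of controls and 21% of treated patients would exceed a 100% reduction, which is impossible. The cap deals with this roughly, and the direction survives, but the largest gaps should not be taken as forecasts.

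**Conclusion.** The point holds in limited form. The one analysis assigned to the TCM syndrome outcome discards the distinction among three of its four grades and, under an ordinary modest shift, has clearly less power than an analysis of data the trial already collects. Under the stated assumptions the power is about 57% down to 31%, against 66–70% for the four grades and 74–77% for the score. The loss is small if the effect is large, or if benefit is concentrated near the 30% line.

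This is a secondary outcome for which no power is claimed, and the choice introduces no bias or false-positive risk. It is a worthwhile, inexpensive improvement. It does not threaten the trial's main conclusion, and it does not show that the responder rate is wrong or should be demoted.

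**What to change.** In the section on secondary efficacy indices, name the TCM syndrome score among the quantitative indices analysed by GLMM, using months 3, 6, 9 and 12 and adjusting for the month-0 score. Alternatively, compare the four defined grades with a proportional-odds GEE. Keep the total effective rate as the reported responder analysis, with its between-group comparison restricted to months 3 to 12.

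The cost is about one sentence, with no new data or visits and a model already planned for other indices. The downsides are one additional secondary test, and a mean difference or common odds ratio that TCM readers will find less familiar than the total effective rate.

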#### Data analysis of quality of life

The SCL-90, SF-36, SAS scale, and SDS scales will be used to measure the quality of life of subjects in both groups when each of the patients will visit a study center during the continuous time points of the study (0, 3, 6, 9, and 12 months). All data are quantitative and GLMM will be conducted to explore the differences in indices between the two groups.

